#### Who will take informed consent? {26a}

The first author will enroll participants, will explain the purpose and process of intervention, and will obtain informed consent in both qualitative and intervention stages.

#### Additional consent provisions for collection and use of participant data and biological specimens {26b}

Participants will be requested to complete the consent form which includes items regarding consent to complete the questionnaire and consent to participate in the intervention: There are no charges from participants; they may withdraw or take away their permission to use the information at any time by sending a written notice to the researcher. If they withdraw their permission, they will exit the study. If necessary, any changes in the protocol modifications will be made with the consent of all authors and then, if finalized, will communicate to participants. There will be HbA1C test before and after the intervention.

### Interventions

#### Explanation for the choice of comparators {6b}

The designed intervention will be carried out only by the intervention group and the control group will only receive routine clinical care. The control group will receive training at the end of the study.

#### Intervention description {11a}

The intervention will be designed based on HPM constructs for T2D patients. The emphasis of the intervention materials will be on predictors of behavior that have been identified based on the need assessment and a pre-test that will be performed using the researcher-made questionnaire. The first author will recruit participants, will explain the purpose and process of intervention, and will obtain their informed consent to participate. According to the intervention program, the participants will not receive any other relevant education or training during the intervention. Sessions will present by one health education and promotion specialist and one internal specialist medicine, experienced in T2D treatment adherence. Intervention including 10 educational sessions in groups of 15 to 20 patients will be a combination of online and face-to-face methods according to the intervention group conditions. The intervention will be using challenging lectures, educational video clips, posters and pamphlets, and the main content of the sessions will be to promote and improve adherence to treatment in the areas of medication, diet, and physical activity. In-person sessions will be set to an average of 45 min and online sessions to 15 min. The control group will receive training at the end of the study.

#### Criteria for discontinuing or modifying allocated interventions {11b}

Leaving the study at any time by the participants will not affect the quality of services received in the diabetic clinic. Study participant collected data will be included in the analysis.

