#### Intervention stage

Eligible participants will be women or men, over the age of 80, need to express their consent to participate in the research and have registered a medical case in the Diabetes Clinic of Shahid Mohammadi Hospital as a patient with T2D and also live in Bandar Abbas.

The exclusion criteria also include participating in intervention sessions (absence of more than two interventional sessions) and not referring to the Diabetes Clinic of Shahid Mohammadi Hospital.

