#### Outcomes {12}

The primary outcome is treatment adherence which will be measured according to score of the researcher-made questionnaire and HbA1c test before and 3 months after the intervention. Secondary outcomes include attendance at clinic appointments, weight, healthy diet days, and physically active days.

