#### Plans to promote participant retention and complete follow-up {18b}

Researchers will be in contact with participants through SMS and phone calls.

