#### Methods in analysis to handle protocol non-adherence and any statistical methods to handle missing data {20c}

In case of missing outcome data, the study analyses will be according to available data, relying on an assumption that data is missing at random. Reasons for missingness will be described by a chart, and frequency of miss patients for each stage will be described.

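### The rule on leavers' data makes no exception for revoked permission, and stopping the sessions is not separated from leaving the study

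*Protocol article*

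**What the plan says.** Four places in the protocol article bear on this.

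- **Consent provisions {26b}.** Participants are told that "they may withdraw or take away their permission to use the information at any time by sending a written notice to the researcher". The consequence is given next: "If they withdraw their permission, they will exit the study". The section does not say what happens to data already collected from such a person.
- **Discontinuing or modifying the intervention {11b}.** The whole text is two sentences: "Leaving the study at any time by the participants will not affect the quality of services received in the diabetic clinic", and then "Study participant collected data will be included in the analysis". It gives no criteria for stopping the sessions and no exception for revoked permission.
- **Eligibility criteria {10}, intervention stage.** The exclusion criteria include "absence of more than two interventional sessions". The text does not say whether such a person is excluded from further sessions, from follow-up or from the analysis.
- **Missing data {20c}.** Where outcomes are missing, "the study analyses will be according to available data, relying on an assumption that data is missing at random".

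The primary outcome {12} is treatment adherence, from the questionnaire score and the "HbA1c test before and 3 months after the intervention". The retention plan {18b} reads: "Researchers will be in contact with participants through SMS and phone calls".

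**The concern.** There are two separate problems.

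The first concerns consent. A participant who takes back permission to use the data becomes a leaver under {26b}, and {11b} sends leavers' data to the analysis. The team must then either use data whose use the participant has withdrawn, or drop data that {11b} says to include. The trial is open-label and the statistician is not blinded {17a}, so that choice could be made knowing the arm.

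The second concerns follow-up. A participant who tires of the sessions need not leave the study, but the protocol does not keep the two apart, and the absence criterion points towards removal. During the study only the intervention arm has sessions to miss; the control arm is trained after the study ends {6b}. Any removal for absence is therefore one-sided. It plausibly falls on the less adherent patients, in a trial whose outcome is adherence. An available-data analysis that assumes missing at random does not correct for this if the loss depends on adherence that was not observed.

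**Working it through.** **1. The sections set side by side**

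| Participant | {26b} | {11b} | {10} |
|---|---|---|---|
| Revokes permission to use data | Exits; use of the information no longer permitted | Collected data included | Silent |
| Leaves without revoking | May withdraw | Collected data included | Silent |
| Misses more than two sessions, does not ask to leave | Silent | Silent | Excluded; from what is not stated |

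Row 1 is the conflict, and no other section resolves it: {20c} deals with missing outcomes, not with data that exist but may not be used. Row 2 is consistent, and including those data is proper. Row 3 is a gap in {11b}, with an exclusion in {10} that cannot act before the sessions begin, hence not before randomisation.

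**2. The plan's own figures {14}**

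Inputs: SD 29.7, difference 13.5, two-sided 5%, power 80%, 10% drop-out, 83 per group.

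- Standard two-sample formula: n = 2 × [29.7 × (1.960 + 0.842) / 13.5]² = 75.98, so 76 per group. This reproduces the stated figure.
- Drop-out: 76 × 1.10 = 83.6, and 76 / 0.90 = 84.4, rounded up to 85. The stated 83 is within two patients of either.
- Expected loss: 0.10 × 83 = 8.3 per group, 16.6 of 166 overall.

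**3. Power is not the main issue**

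From 83 per group, power is 83.4% with no loss, 79.3% with 10% loss in both arms, and 81.3% with 10% loss in the intervention arm only. One-sided loss at the planned rate costs about 2 percentage points.

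**4. Illustration of the bias from one-sided loss**

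Let p be the fraction lost from the intervention arm and D the amount by which those lost score below those kept. The observed arm mean exceeds the mean of everyone randomised to that arm by p × D.

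- p = 8/83 = 0.096 (the planned drop-out rate; loss in this arm only is an assumption).
- D = 20 to 30 points (an assumption; 20/29.7 = 0.67 SD and 30/29.7 = 1.01 SD).
- Shift: 0.096 × 20 = 1.9 points; 0.096 × 30 = 2.9 points.
- Relative to 13.5 points: 14% to 21%.

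The shift favours the intervention, because the low scorers are the ones missing. This calculation concerns row 3 of the table. It does not measure row 1, for which the documents give no number.

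**The case against.** The strongest reply is that the two sections can be read together. {11b} is a general sentence on keeping data already collected, {26b} is the specific rule for revocation, and a specific rule limits a general one. {26b} also only summarises the consent form, which is not shown and may settle the matter. This has weight: it cannot be shown that data would in fact be used against consent. But {11b} states its rule flatly and {26b} does not say what happens to collected data, so a reader has to supply the exception. That should be written down.

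A reader might go further and infer that {11b} treats stopping the programme as leaving the study, so that no 3-month measurement is due. The text does not support this. {11b} does not equate the two; it only fails to separate them. The 3-month measurement applies to both groups with no exemption for people who stop sessions. A missed session prompts a phone call {11c}, not an exit, and {18b} plans continued contact. Loss of follow-up is therefore a risk, not a stated consequence. What remains is the absence criterion in {10}, and the lack of any statement that a person who meets it is still measured.

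A reader might also infer that leavers' data should not be analysed at all. That is wrong for anyone who leaves without revoking permission.

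The bias figure is fairly open to challenge. It puts all the loss in one arm, although {14} allows 10% in each, and it assumes a large deficit among those lost. Analysis of covariance, listed in {20a}, could absorb part of such a deficit if it is already visible at baseline.

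**Conclusion.** The point holds in two limited parts. First, {11b} lacks an exception for participants who revoke permission under {26b}, and the two sections must be reconciled. The number affected is unknown and may well be small, but the question is one of consent and does not depend on that number. Second, {11b} does not distinguish stopping the sessions from leaving the study, while {10} lists session absence as an exclusion that can act only after randomisation and only in the intervention arm. If it is applied to follow-up or analysis, it removes non-attenders from one arm.

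The shift of roughly 2 to 3 points is an illustration near the unfavourable end. It rests on all 8 losses falling in the intervention arm, a deficit of 20 to 30 points, and no recovery through baseline adjustment. It is neither a forecast nor a measure of the consent conflict. The point should be corrected; it does not undermine the design as a whole.

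**What to change.** Rewrite {11b} to cover three cases, and align {10} and {26b} with it.

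1. **Stops or misses sessions.** The participant stays in the study, is invited to the 3-month questionnaire and HbA1c test, and is analysed in the allocated arm. Remove the absence criterion in {10} as a ground for exclusion from follow-up or analysis; attendance can still be recorded and reported.
2. **Leaves the study without revoking permission.** Data collected up to that date are kept and analysed.
3. **Revokes permission to use data.** The participant is handled as the consent terms state, and counted by arm in the chart of missingness that {20c} already plans. Since {26b} is silent on data already collected, check that the consent form answers this, and repeat the answer in {11b}.

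The cost is wording in three sections, a check of the consent form, and one field on the record form for the case and date. The practical downside is a few extra contact attempts for people who stop attending.

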#### Strategies to improve adherence to interventions {11c}

The researchers will send intervention session reminders to the participants via short message service (SMS) and will be in touch with them. In case of missing sessions, the first author will contact the participant by phone call.

#### Relevant concomitant care permitted or prohibited during the trial {11d}

Relevant intervention or training during the intervention is prohibited. Usual routine clinical care health care is permitted during the study.

#### Provisions for post-trial care {30}

This is not applicable as there is no anticipated harm and compensation for trial participation.

#### Outcomes {12}

The primary outcome is treatment adherence which will be measured according to score of the researcher-made questionnaire and HbA1c test before and 3 months after the intervention. Secondary outcomes include attendance at clinic appointments, weight, healthy diet days, and physically active days.

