**Methods:**

This mixed method study will consist of qualitative stage, questionnaire design and a randomized, open-label, parallel-group interventional study based on HPM in southern Iran. Sampling for qualitative stage will continue until reaching the saturation. In the intervention stage, participants will be 166 T2D patients referring to the Bandar Abbas Diabetes Clinic will be randomized into intervention and control groups (allocation 1:1). After identifying the factors affecting adherence to treatment in T2D patients by qualitative study and literature review, a questionnaire based on HPM will be designed. In the next stage, 10 sessions of intervention for the intervention group will be designed. To evaluate the effect of the intervention, intervention and control groups will be tested for hemoglobin A1c (HbA1c) before and 3 months after the intervention.

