#### Intervention stage

When designing the educational intervention, the two intervention and control groups will be selected from T2D patients with registered medical cases in the Diabetes Clinic of Shahid Mohammadi Hospital in Bandar Abbas. According to previous study [19], the pooled standard deviation is calculated to be 29.7. Also, assuming a type I error = 5%, test power = 80%, and also considering a 13.5-score difference in adherence to treatment of the intervention and control group, the sample size of each group is estimated to be equal to 76 [20]. Considering the 10% possible drop-out, the sample size is determined 83 people in each of the two groups.$$n=\frac{2{\left({z}_{1-\frac{a}{2}}^2+{z}_{1-\beta}\right)}^2{s}_p^2}{{\left({\mu}_1-{\mu}_2\right)}^2}=76$$

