### Statistical methods

#### Statistical methods for primary and secondary outcomes {20a}

Data analysis will be performed using SPSS ver.26. To describe the quantitative variables, descriptive statistics will be conducted. In the intervention phase, independent *t*-test, paired *t*-test, and analysis of covariance are used to evaluate the effectiveness of the intervention on changing the behavior and HPM constructs.

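### One primary outcome is defined by two measures, the adherence score and HbA1c, with no rule for which decides, while the sample size serves only the score

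*Protocol article*

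**What the plan says.** Four places in the protocol article bear on what decides the trial.

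- Outcomes {12} sets a single primary outcome with two measures: "The primary outcome is treatment adherence which will be measured according to score of the researcher-made questionnaire and HbA1c test". Both are taken at baseline and again at 3 months. No combination, order or success rule follows.
- Sample size {14}, Intervention stage, works on the score only: "considering a 13.5-score difference in adherence to treatment of the intervention and control group", where "the pooled standard deviation is calculated to be 29.7". The error rates are set by "assuming a type I error = 5%, test power = 80" (per cent), and "the sample size of each group is estimated to be equal to 76". No HbA1c difference or SD is given.
- The abstract's Methods paragraph says that, to evaluate the effect, "intervention and control groups will be tested for hemoglobin A1c (HbA1c) before and 3 months after the intervention". Trial design {8} has a near-identical sentence. Neither sentence mentions the questionnaire score.
- Statistical methods {20a} lists the independent and paired t-tests and analysis of covariance, used to assess the "effectiveness of the intervention on changing the behavior and HPM constructs". HbA1c is not named there.

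**The concern.** The score and HbA1c are different kinds of variable on different scales. One is a questionnaire answered by participants who know their allocation (blinding section {17a}), and the other is a laboratory value. A programme built on the health promotion model could move the score without moving HbA1c within 3 months, or the reverse. In either case {12} does not say whether the trial has succeeded.

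The other sections do not settle it. Sample size {14} points to the score, while the abstract and {8} point to HbA1c. The choice of primary outcome fixes the sample size and belongs in the protocol, so it cannot be regarded as detail left to a later analysis plan. Such a plan could resolve the matter only by choosing between statements the protocol already makes. At stake is whether the stated 5% type I error and 80% power describe the trial's actual success criterion.

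**Working it through.** **Inputs from Sample size {14}:** difference 13.5, SD 29.7, two-sided α = 0.05 (from the 1 − α/2 quantile in the formula), power 0.80, allocation 1:1.

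**1. Reproduce the plan's figure.** With the standard formula,

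n = 2(z₀.₉₇₅ + z₀.₈₀)² × SD² / difference² = 2 × (1.960 + 0.842)² × 29.7² / 13.5² = 75.98, so 76 per group.

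This matches. (The printed formula squares the first quantile inside the bracket. Read literally it gives about 212, so that is a typesetting slip.) The figure is obtained from the score inputs alone at an undivided 5%, and HbA1c does not enter.

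**2. What each possible rule would imply.** The document states none of these rules, so the results are conditional.

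*(a) Score as sole primary.* Type I error 5%, power 80%, 76 per group. The statements in {14} hold as written.

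*(b) Either measure at 5% is enough.* Family-wise error is 1 − P(|Z₁| < 1.96 and |Z₂| < 1.96). If independent it is 1 − 0.95² = 0.0975. For correlated tests a bivariate normal is used; the correlations are assumptions. With a Bonferroni split (α = 0.025 each), the score would need 93 per group before drop-out, and power for the score at 76 per group would be 0.71.

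*(c) Both must be significant.* There is no inflation of type I error, but power falls. If each test had 80% power, joint power is 0.8 × 0.8 = 0.64 under independence. Joint power of 80%, under independence and equal power, requires √0.8 = 0.894 for each test, which is 100 per group for the score.

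| Correlation between the two tests (assumed) | (b) Family-wise error | (c) Joint power, 80% each |
|---|---|---|
| 0 | 9.75% | 64% |
| 0.3 | 9.5% | 67% |
| 0.5 | 9.1% | 69% |
| 0.8 | 7.8% | 73% |

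*(d) HbA1c as sole primary.* The document gives no HbA1c difference or SD, so its power cannot be calculated. In SD units, 76 per group detects √(2/76) × (1.960 + 0.842) = 0.454 SD with 80% power in an unadjusted comparison. The table takes assumed SDs of 1.0 to 2.0 percentage points. The adjusted column uses analysis of covariance with an assumed baseline correlation ρ of 0.5 to 0.7, which multiplies the detectable difference by √(1 − ρ²), that is by 0.866 to 0.714.

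| Assumed SD | Detectable, unadjusted | Detectable, adjusted for baseline | Power for an assumed 0.5-point difference, unadjusted |
|---|---|---|---|
| 1.0 | 0.45 | 0.39 to 0.32 | 87% |
| 1.5 | 0.68 | 0.59 to 0.49 | 54% |
| 2.0 | 0.91 | 0.79 to 0.65 | 34% |

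**3. Comparison.** Only rule (a) delivers the stated 5% and 80% together from the information in {14}. Outcomes {12} does not state rule (a).

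**The case against.** The strongest reply is that the divergence is loose wording. Statistical methods {20a} is headed as covering primary and secondary outcomes, {12} makes HbA1c part of the primary outcome, and t-tests and analysis of covariance suit a continuous HbA1c value. The same section does not name weight or clinic attendance either. This stands. A reader might infer that HbA1c has been left out of the analysis, but the text shows only that it is not named.

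The sentences in the abstract and {8} likewise omit the score without saying that HbA1c alone decides, and {8} also describes a questionnaire built to measure adherence. They can coexist with {12}, but they do not supply a rule.

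It is also fair to say that the error and power figures depend on rules the protocol never adopts. A reader might infer that the trial runs at 9.75% type I error or has 64% power. Neither is a property of this plan: the first needs an either-measure rule, the second a both-measures rule and 80% power for HbA1c, and both assume independence. A reader might also expect the investigators to pick the self-reported score after the fact. Nothing in the document supports that prediction.

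Finally, the score is an awkward choice of sole primary. It is an unblinded self-report, the questionnaire is still to be designed (Questionnaire design, under {18a}), no total or subscale is identified as the adherence score, and the SD comes from a previous study. This stands as a limit on the fix. It does not remove the need to choose.

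**Conclusion.** The point holds: {12} places two distinct measures under one primary outcome and gives no decision rule, and {14} powers only one of them. The 5% and 80% in {14} are jointly valid only if the score is the sole primary outcome, which the protocol does not say.

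The size depends on the rule eventually adopted. Over the correlations checked (0 to 0.8), an either-measure rule would give a type I error of 7.8% to 9.75%. A both-measures rule would keep the error at or below 5% but give joint power of 64% to 73%, provided HbA1c itself had 80% power, which the document does not allow one to verify. The arithmetic in {14} is not at fault for the score. Because the success criterion is undefined and the repair is cheap, this should be fixed before any outcome data are seen.

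**What to change.** In {12} and {20a}, name one primary outcome. The choice that leaves {14} unchanged is the adherence score at 3 months, with the total or subscale identified, tested at two-sided 5%. HbA1c at 3 months would then be the key secondary outcome, tested at 5% only if the score is significant (fixed sequence), and analysed by analysis of covariance on baseline HbA1c. Bring the abstract and {8} into line with {12}, and update the registry entry.

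The cost is wording only, with no added patients. The statistical price should be stated openly: if the score is not significant, no confirmatory claim on HbA1c is possible, although HbA1c is the measure that the abstract and {8} put forward.

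If the sponsor wants HbA1c to count as primary, the protocol should instead state the rule (both required, or a split α) and restate power in {14} with an HbA1c difference and SD. That may raise the sample size. For the score alone, before drop-out, the figure would be 93 per group under a Bonferroni split, or about 100 per group for 80% joint power under independence and equal power.

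### Clinic attendance is a secondary outcome, yet not coming to the same clinic is an exclusion criterion; on the likelier reading, effects on dropping out of clinic care are reduced or lost

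*Protocol article*

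**What the plan says.** Under Outcomes {12} the protocol article lists: "Secondary outcomes include attendance at clinic appointments, weight, healthy diet days, and physically active days".

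Under Eligibility criteria {10}, Intervention stage, the exclusion criteria include "absence of more than two interventional sessions) and not referring to the Diabetes Clinic of Shahid Mohammadi Hospital". The inclusion criteria in the same section already require that patients "have registered a medical case in the Diabetes Clinic of Shahid Mohammadi Hospital as a patient with T2D".

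Three other statements bear on what happens to a patient who stops coming:

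- Section {11b}, on participants leaving the study: "Study participant collected data will be included in the analysis".
- Section {20c}, on missing data: "In case of missing outcome data, the study analyses will be according to available data, relying on an assumption that data is missing at random".
- Section {26b}, on withdrawal of permission to use information: "If they withdraw their permission, they will exit the study".

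No section says how attendance is scored for a patient who stops coming, or where the attendance data come from.

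**The concern.** The same behaviour at the same clinic is both something the trial measures and a reason for exclusion. If the criterion is applied after randomisation, the patients with the lowest attendance leave the comparison because of their value on the outcome.

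The programme could help patients stay in clinic care, or could discourage them through the burden of ten sessions. Either effect would show largely as a different share of patients in each arm who stop coming. Removing those patients takes that share out of the comparison, in whichever direction it runs. It also makes average attendance look better than it was in both arms.

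**Working it through.** **Is the exclusion a screen at entry or a removal rule?**

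- Its neighbour in the sentence, absence from more than two sessions, cannot occur before allocation.
- Registration at the clinic is already needed for entry, so as an entry screen the criterion would add little.
- Section {11b} keeps the collected data of participants who leave. That conflicts with removal, but it does not say that appointments missed later count as not attended.

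Removal after randomisation is therefore the likelier reading, but it is not explicit.

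**Does the missing-data rule in {20c} add to the problem?** It applies only where outcome data are missing. A patient who stops coming has a low attendance value that can be observed from records. The rule would drop that patient only if non-attendance were coded as missing. In that case missingness would depend on the outcome itself and missing at random would not be credible. The text does not state such coding.

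**Inputs.** The protocol gives 83 patients per arm and 10% drop-out (Sample size {14}). Its only sample size is for the adherence score: 2 × (1.960 + 0.842)² × 29.7² / 13.5² = 75.98, which reproduces the stated 76 per group and has no bearing on attendance. The protocol gives no attendance or stopping rate, so the following are assumptions:

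- *m*, the share of appointments kept by patients who continue: 70% to 90%
- *c* and *t*, the shares who stop in the control and intervention arms
- *k*, attendance of stoppers relative to continuers: 0 unless stated

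**Formulas.** With everyone kept, the mean in an arm with stopping share *s* is m × (1 − s + s × k). With equal *m* in both arms, the difference is m × (1 − k) × (c − t). After stoppers are excluded, both means equal *m* and the difference is 0.

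**Level of attendance.** Suppose the planned 10% drop-out all stop coming, with k = 0. Mean attendance is then 0.90 × 70% = 63% to 0.90 × 90% = 81%. After exclusion it would be reported as 70% to 90%, which is 7 to 9 points too high.

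**Difference between arms.**

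| Stopping, control v intervention | m | k | All randomised | Stoppers excluded |
|---|---|---|---|---|
| 15% v 5% | 70% | 0 | 7 points | 0 |
| 15% v 5% | 80% | 0 | 8 points | 0 |
| 15% v 5% | 90% | 0 | 9 points | 0 |
| 15% v 5% | 70% to 90% | 0.5 | 3.5 to 4.5 points | 0 |
| 5% v 15% | 80% to 90% | 0 | −8 to −9 points | 0 |

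**If continuers also differ.** Take 80% (control) v 85% (intervention) among continuers, with k = 0. With 15% v 5% stopping the full difference is 0.95 × 85% − 0.85 × 80% = 12.75 points. With 20% v 5% it is 0.95 × 85% − 0.80 × 80% = 16.75 points. After exclusion, 5 points remain in both cases.

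**Power, same kind of illustration.** Take 83 per arm, m = 80%, SD 15 points among continuers, 15% v 5% stopping and k = 0.

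- Control variance: 0.85 × 0.15² + 0.85 × 0.15 × 0.80² = 0.1007
- Intervention variance: 0.95 × 0.15² + 0.95 × 0.05 × 0.80² = 0.0518
- Standard error: √[(0.1007 + 0.0518)/83] = 0.0429
- Ratio: 0.08/0.0429 = 1.87, so two-sided power at 5% is about 46%

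After exclusion the expected difference is 0, so a test rejects at about its nominal 5%. That second figure follows from assuming no effect among continuers.

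**The case against.** **The criterion may be an entry screen.** The article often speaks of patients referring to the clinic to describe its source population. The clinic has 1500 registered patients (Study setting {9}), and some may no longer attend, so the criterion could identify people who are not current patients at entry. It also gives no threshold for how much missed attendance leads to exclusion. This stands as a possible reading, but the session-absence criterion beside it makes it the less likely one.

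**Section {11b} keeps collected data.** This stands as evidence against removal. It leaves two sections in tension and still does not settle how later missed appointments are scored.

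**The missing-data rule is not at fault.** A reader might infer that {20c} would drop these patients even if the exclusion were deleted. The documents do not support that: a patient with an observed low value is not missing, and nothing says attendance is set to missing when a patient stops coming.

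**The numbers are constructed.** This also stands. The stopping rates, their split between arms, the zero score and the absence of an effect among continuers are all assumptions. The planned drop-out is drop-out from the trial, which need not mean leaving clinic care.

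**Scoring detail belongs in the full protocol or analysis plan.** This is fair for the numerator, denominator and time window. It does not cover an exclusion criterion in the published text that overlaps with a named outcome.

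**Conclusion.** The point holds in a limited form. The exclusion criterion and the attendance outcome rest on the same behaviour, and on the likelier reading the criterion removes randomised patients for it. The comparison would then be biased for any effect on dropping out of clinic care.

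A reader might go further and infer that the outcome can never record poor attendance, or that every effect on attendance is hidden. The text does not support this. Appointments missed by patients who remain still count, {11b} may keep what was recorded before a patient left, and in the example with 80% v 85% among continuers a 5-point difference survives exclusion.

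The size is unknown, because the documents give no rates. With 15% v 5% stopping, stoppers at zero and 70% to 90% attendance otherwise, 7 to 9 points become 0; if stoppers kept half as many appointments as the others, 3.5 to 4.5 points become 0. The outcome is secondary and the stated sample size is unaffected. The wording should be corrected.

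**What to change.** Reconcile Eligibility criteria {10}, {11b} and {20c} as follows:

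1. State that not coming to the clinic does not remove a randomised patient from the analysis. If the criterion is meant only as a screen at entry, say so.
2. Define attendance as appointments kept divided by appointments scheduled, taken from the clinic's registered files for all 166 randomised patients.
3. Count appointments missed after a patient stops coming as not attended, not as missing. The exception is a patient who has withdrawn permission to use the data ({26b}).

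The cost is a sentence or two and a look-up in files the clinic already holds. There is a small downside: reported attendance will look less favourable, and a patient who moves to another clinic counts as not attending.
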